## Trial design {8}

This multicentre study is designed as a double-blind, placebo-controlled, randomised, clinical superiority trial. Randomisation will be performed with a 1:1 allocation ratio.

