### Sample size {14}

In the Netherlands, approximately 50% of patients with cSDH is primarily treated conservatively [7]. Of these, 75% still need surgery (own data). Since oral TXA is an innovative treatment in these patients, little data is available concerning its efficacy. Until today, only five small studies, concerning a total of 39 patients treated with TXA, have been published [12–16]: none of these patients required surgery after the start of treatment. As this 100% reduction of surgery may well be an over-estimation of the true effect, a conservative estimate of 33% relative risk reduction was used in the sample size calculation (from 75% surgery in the placebo group to 50% surgery in the TXA group). A Fisher’s exact test with a 0.05 two-sided significance level will have 80% power to detect the difference between a control (placebo) group proportion of 0.75 and a treatment (TXA) group proportion of 0.50 when the sample size in each group is 64 (128 patients in total).

We consider the quality of life (QoL), measured with the SF-36, as an important secondary functional outcome indicator. With a sample size of 64 patients per treatment arm, we are also able to detect a Cohen’s *d* effect size (difference between the mean SF-36 scores of the control group and treatment group divided by the pooled SD) of 0.50. Although an effect size of *d* = 0.50 can be defined as ‘moderate’ [33], such a difference in mean QoL scores may be clinically important. Anticipating an attrition rate of about 8%, we will include 70 (64/0.92) patients in each group (140 patients in total).

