## Statistical methods

### Statistical methods for primary and secondary outcomes {20a}

Statistical analyses will be based on the intention-to-treat principle. Baseline assessments and outcome parameters will be summarised using simple descriptive statistics. Continuous, normally distributed variables will be expressed as means and standard deviations; continuous, non-normally distributed and ordinal variables as medians (25th–75th percentiles), and categorical variables as counts and percentages. Normality of data will be explored by a normal Q-Q plot and tested by the Shapiro-Wilk test. Where necessary we will use multiple imputations for handling missing data. In all analyses, statistical uncertainty will be expressed in two-sided 95% confidence intervals. A two-sided *p* value less than 0.05 is considered statistically significant. We will not correct for multiple testing.

The difference in the proportion of patients requiring surgery for cSDH within 12 weeks after the start of treatment will be analysed using Fisher’s exact test. In addition, logistic regression will be performed including treatment groups, stratification variables and baseline variables (if large differences exist between treatment groups) as independent variables. The effect size will be expressed in an adjusted odds ratio.

Differences in volume reduction of cSDH, neurological impairment (mNIHSS) and cognitive function (MOCA) between the treatment groups and overall time points will be analysed using a linear mixed model with treatment group membership as a fixed-effect and an appropriate random-effect structure. The number of falling incidents and mortality rate during the 12 weeks (and 6 months) follow-up will be analysed using Fisher’s exact test. ADL scores (Barthel Index and Lawton-Brody scale) and functional outcome score (mRS) at 12 weeks (and 6 months) will be compared with the two-sample *t*-test or Mann-Whitney test, where appropriate. Differences in the mean changes in the level of quality of life (SF-36) from baseline to 12 weeks (main secondary outcome) (and 6 months) will be analysed using the two-sample *t*-test. In addition, we will analyse these treatment effects by performing multivariable linear regression with treatment groups, the baseline values and the stratification variables as the independent variables.

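### The SF-36 detectable effect is stated for scores, but the leading test uses change from baseline; the planned baseline-adjusted regression fits the claim better and should lead

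*Protocol article*

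**What the plan says.** The Sample size section of the protocol article sizes the trial on the primary endpoint. A Fisher's exact test at 64 per arm "will have 80% power to detect the difference between a control (placebo) group proportion of 0.75" and a TXA proportion of 0.50. It then turns to quality of life: "With a sample size of 64 patients per treatment arm, we are also able to detect a Cohen’s" effect size of 0.50. That effect size is defined as the "difference between the mean SF-36 scores of the control group and treatment group divided by the pooled SD". No power is attached to this SF-36 statement, and no SF-36 SD or baseline correlation is given.

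The Statistical methods section names the analysis of the same outcome. "Differences in the mean changes in the level of quality of life (SF-36) from baseline to 12 weeks (main secondary outcome") are to be compared by a two-sample t-test. The next sentence adds a second analysis of the same treatment effects, "performing multivariable linear regression with treatment groups, the baseline values and the stratification variables as the independent variables". It is introduced as additional, so the t-test on change comes first.

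**The concern.** A change from baseline and a score at 12 weeks have different SDs. Under randomisation both analyses target the same difference between arms, because baseline means are equal in expectation. A detectable effect worked out with the SD of a score therefore carries over to a test on change only if the two SDs match. The article makes the claim on one scale and tests on the other, with nothing to link them.

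It also plans two analyses of its main secondary outcome and puts the one that is generally less precise first. If the two fall on opposite sides of the 5% level, the order in the text decides which result carries the weight.

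**Working it through.** **Inputs from the protocol article**
- Evaluable patients per arm: 64, d = 0.50 (Sample size).
- Two-sided 5% level: "A two-sided *p* value less than 0.05 is considered statistically significant" (Statistical methods).
- Equal arms: "Randomisation will be performed with a 1:1 allocation ratio" (Trial design).

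**Assumptions, not in the article**
- 80% power for the SF-36, carried over from the primary endpoint.
- Equal SDs at baseline and 12 weeks, set to 1.
- r unknown, shown from 0 to 0.8.

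**Step 1. Reproduce the plan's figure on the score scale.** The noncentrality is d × √(n/2) = 0.50 × √32 = 2.83. The exact two-sample t-test power is 80.1% at 64 per arm and 79.5% at 63. The claim of 64 per arm for d = 0.50 therefore reproduces for a t-test on scores at 80% power.

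**Step 2. Put both planned analyses on the same footing.**
- SD of change = √(2(1 − r)).
- Residual SD after baseline adjustment = √(1 − r²).

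Example at r = 0.3:
- Change: SD = √1.4 = 1.183; standardised effect 0.50/1.183 = 0.423; power 66.0%.
- Regression: SD = √0.91 = 0.954; standardised effect 0.50/0.954 = 0.524; power 83.7%.

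**Step 3. Full range**, 64 per arm. Power is for a true difference of 0.50 score SD; detectable effects are at 80% power, in score SDs.

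| r | Power, t-test on change | Detectable effect, change | Power, baseline-adjusted regression | Detectable effect, regression |
|---|---|---|---|---|
| 0 | 51.0% | 0.71 | 80.1% | 0.50 |
| 0.2 | 60.2% | 0.63 | 81.7% | 0.49 |
| 0.3 | 66.0% | 0.59 | 83.7% | 0.48 |
| 0.4 | 72.7% | 0.55 | 86.5% | 0.46 |
| 0.5 | 80.1% | 0.50 | 90.0% | 0.43 |
| 0.6 | 88.1% | 0.45 | 93.9% | 0.40 |
| 0.7 | 95.2% | 0.39 | 97.6% | 0.36 |
| 0.8 | 99.3% | 0.32 | 99.7% | 0.30 |

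The regression column ignores the small cost of estimating the covariate coefficients. That matters only near r = 0, where the figure sits on 80% itself.

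**Step 4. Break-even for the t-test on change.** With equal SDs, √(2(1 − r)) ≤ 1 requires r ≥ 0.5. With unequal SDs, and d standardised by the 12-week SD, the condition is SD_baseline² + SD_12wk² − 2r × SD_baseline × SD_12wk ≤ SD_12wk². This gives r ≥ SD_baseline/(2 × SD_12wk). As an illustration, a 12-week SD 1.2 times the baseline SD lowers the threshold to 1/2.4 = 0.42; a smaller 12-week SD raises it above 0.5.

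**Step 5. Compare the two analyses at any r.** With equal SDs, the variance of the regression estimate over that of the change estimate is (1 − r²)/(2(1 − r)) = (1 + r)/2. This is below 1 for every r < 1, so the preferred order does not depend on the unknown correlation.

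**The case against.** A reader might infer that the trial is underpowered for its main secondary outcome. The article does not support that. It gives no r, and above 0.5 the t-test on change has more power than the claim implies: 88% to 99% at r = 0.6 to 0.8. Nor does the text settle which side of 0.5 is likely. Most placebo patients are expected to have surgery between the two assessments, which could weaken the correlation. Against that, the eligibility criteria require mild symptoms and a stable deficit, and a large average change does not lower r unless patients change by differing amounts.

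Other objections also carry weight:
- The efficient analysis is already planned for the same treatment effects, so d = 0.50 is detectable in a prespecified analysis whatever non-negative value r takes.
- The article calls the regression additional; it does not call it supportive. The primary outcome follows the same pattern, with an unadjusted test and then an adjusted model.
- Both analyses are valid under randomisation. The choice between them concerns precision, not bias.
- The SF-36 sentence is a by-product of a sample size set by the primary endpoint and states no power of its own.

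These points limit the size of the issue. They do not remove the mismatch of scales, or the reason to put the more precise analysis first.

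**Conclusion.** The point holds as a minor inconsistency with a free improvement. The detectable effect is worded for scores, while the analysis named first tests change. For that test, with equal SDs and 80% power assumed, the d = 0.50 figure holds only if r ≥ 0.5. The condition does not apply to the regression, which meets the figure at essentially any r ≥ 0.

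The stronger conclusion, that the implied power will not be delivered, is not shown: r is unknown, and the t-test could fall short of 80% or exceed it. What can be said without knowing r is that, with equal SDs, the regression is the more precise analysis at every r < 1. Putting it first brings the analysis into line with the sample-size statement and settles which result leads.

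**What to change.** In Statistical methods for primary and secondary outcomes, name the linear regression of the 12-week SF-36 on treatment group, baseline value and stratification variable (anticoagulant and/or antiplatelet use) as the main analysis of this outcome. Keep the two-sample t-test on change as supportive.

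In Sample size, state that d = 0.50 refers to the 12-week score, and give the power (80% at 64 per arm for a two-sided 5% t-test on scores).

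If the sponsor prefers to keep the t-test on change in front, the alternative is to state the assumed correlation or to define d on the change scale.

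The cost is a few words and the re-ordering of two analyses already planned. The sample size, the visits and the data collected stay as they are.

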### Interim analyses {21b}

A Data and Safety Monitoring Board (DSMB) will perform an interim analysis to monitor safety data and sample size assumptions when follow-up is completed of the first 35 participants, 60 participants and 105 participants. In this analysis, unblinded data are assessed and the DSMB can advise to adjust the conduct, design or sample size or to terminate the study.

### Methods for additional analyses (e.g. subgroup analyses) {20b}

Additional analyses are described in the yet to be published statistical analysis plan (SAP).

### Methods in analysis to handle protocol non-adherence and any statistical methods to handle missing data {20c}

Methods in analysis to handle protocol non-adherence and missing data are described in the yet to be published statistical analysis plan (SAP).

### Plans to give access to the full protocol, participant-level data and statistical code {31c}

The datasets analysed during the current study are available from the corresponding author on reasonable request.

### Composition of the data monitoring committee, its role and reporting structure {21a}

The DSMB consists of a statistician/methodologist and two clinicians. All members are independent of the study. Its role is the monitoring of participant safety, the planned sample size assumptions, the efficacy and the overall conduct of the study. Subsequent meetings will be held at 25%, 43% and 75% of trial completion with interim analyses. The DSMB reports directly to the Principal Investigator. Further details can be found in the DSMB charter.

### Adverse event reporting and harms {22}

#### (Serious) adverse events

Adverse events (AE) are defined as any undesirable experience occurring to a subject during the study, whether or not considered related to the investigational product. A serious adverse event (SAE) is any untoward medical occurrence or effect that results in death, is life threatening (at the time of the event), requires hospitalisation or prolongation of existing inpatients’ hospitalisation, results in persistent or significant disability or incapacity, is a congenital anomaly or birth defect or is any other important medical event that did not result in any of the outcomes listed above due to medical or surgical intervention but could have been based upon appropriate judgement by the investigator. An elective hospital admission will not be considered as a serious adverse event.

#### Suspected unexpected serious adverse reactions (SUSAR)

Suspected unexpected serious adverse reactions (SUSAR) are all untoward and unintended responses to an investigational product related to any dose administered. Unexpected adverse reactions are SUSARs if the following three conditions are met: the event must be serious; there must be a certain degree of probability that the event is a harmful and an undesirable reaction to the medicinal product under investigation, regardless of the administered dose; and the adverse reaction must be unexpected, that is to say, the nature and severity of the adverse reaction are not in agreement with the product information as recorded in the Summary of Product Characteristics (SPC).

#### Reporting

Since the largest part of the study period takes place at home, AEs will not directly be observed by the investigator or his staff. Getting knowledge of AEs depends on spontaneous reporting by the subject or other treating physicians to the investigator or his staff. The reported AE will be documented in the patients’ medical file, triaged for being a possible SAE and, if so, handled as such. (S)AEs will be reported during the 12-week study period. If the participant opts in for the optional 6-month telephonic outcome measurement, (S)AEs will be reported during the additional study period between 12 weeks and 6 months after inclusion as well. Each AE will be reported in the CRF. (S)AEs should also be reported to the coordinating investigator/sponsor within 24 h.

The investigator will report all SAEs to the sponsor without undue delay after obtaining knowledge of the events, except for the following:

Hospital admission for the treatment of diseases that can be attributed to being an elderly patient, such as delirium, infections, constipation and an exacerbation of a pre-existent disease (excluding cSDH). These SAEs will be reported in a twice-yearly line listing until the follow-up of the last patient is completed

Hospital admission because of the necessity for surgical treatment of the cSDH. This SAE will be reported in a twice-yearly line listing, since this is the primary endpoint of our study

Except for the abovementioned, the sponsor will report the SAEs through the Web portal ToetsingOnline to the accredited METC that approved the protocol, within 7 days of first knowledge for SAEs that result in death or are life threatening followed by a period of maximum of 8 days to complete the initial preliminary report. All other SAEs will be reported within a period of maximum 15 days after the sponsor has first knowledge of the serious adverse events.

All AEs will be followed until they have abated, or until a stable situation has been reached. Depending on the event, follow-up may require additional tests or medical procedures as indicated, and/or referral to the general physician or a medical specialist.

SUSARs can only be determined by a physician. Therefore, if a trial nurse suspects an SAE to be a SUSAR, the adverse event is presented to the investigator. The investigator judges whether the event must be assessed as a SUSAR. The sponsor will report expeditiously the following SUSARs through the Web portal ToetsingOnline to the METC: SUSARs that have arisen in the clinical trial that was assessed by the METC and SUSARs that have arisen in other clinical trials of the same sponsor and with the same medicinal product and that could have consequences for the safety of the subjects involved in the clinical trial that was assessed by the METC.

The remaining SUSARs are recorded in an overview list (line-listing) that will be submitted once every half year to the METC. This line-listing provides an overview of all SUSARs from the study medicine, accompanied by a brief report highlighting the main points of concern. The expedited reporting will occur not later than 15 days after the sponsor has first knowledge of the adverse reactions. For fatal or life-threatening cases, the term will be maximal 7 days for a preliminary report with another 8 days for completion of the report.

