#### Tranexamic acid

As hyperfibrinolysis is thought to play a role in the liquefaction and enlargement of cSDH, pharmaceutical options to block fibrinolysis have been explored in an effort to eliminate the necessity for surgery [10–16]. The use of tranexamic acid (TXA), an antifibrinolytic drug, has so far been reported in five small series. In the first retrospective series, a total of 21 patients were treated with TXA, of whom three after primary burr hole surgery. In none of these 21 patients, additional surgery was necessary [13]. The second, a prospective pilot study in 14 patients, showed a 41% reduction of cSDH after surgery and an additional 91% residual volume reduction on CT after 90 days during oral TXA treatment of 650 mg per day for a mean (*SD*) duration of 90 (27) days, without recurrence, re-expansion or any complicating venous thromboembolisms [14]. The third study, a case report series of three patients treated with 650 mg TXA per day for 1 month after surgery for cSDH, showed no recurrences and thromboembolic complications [12]. The fourth, a case report of one patient successfully treated primarily with TXA, was recently published [15], and finally, in an Asian article, the authors conclude that administration of Gorei-San, a Japanese herbal Kampo medicine, combined with TXA has the potential to prevent recurrences of cSDH [16].

With these limited, however promising, data, no definitive conclusion can be made regarding the role of TXA in the treatment of cSDH. Therefore, a prospective study evaluating the efficacy and safety of TXA is needed. Currently, two prospective trials (the TRACS study [17] and the TRACE study [18]) are running in an effort to answer this question. The first (TRACS), a phase IIb trial with the aim to provide preliminary data required to plan a larger phase III trial, excludes patients using anticoagulants [17]. These patients comprise a significant portion of the cSDH patient population, and therefore, the results of the TRACS study will be difficult to extrapolate to the future care of all cSDH patients. The second (TRACE) is a randomised, observer-blinded trial, investigating the value of treating cSDH patients with TXA after surgery [18]. In our trial, we plan to include only patients in whom the primary treatment is conservative. Both trials are set up with a primary radiological outcome parameter and therefore potentially provide insufficient clinically relevant information.

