### Strategies to improve adherence to interventions {11c}

Study treatment takes place during the first 4 weeks after inclusion. Follow-up visits take place at 2, 4, 8 and 12 weeks. At inclusion, the participant receives instructions about taking the medication including timing, storage, the importance of taking the capsules whole and what to do in the event of a missed dose. Also, the importance of adherence to the study protocol is discussed. Any leftover study medication is counted during the follow-up visit at 4 weeks. If protocol adherence has been good, the participant should return an empty bottle. Besides these oral instructions, study participants also receive these instructions on paper.

During follow-up visits at 2 and 4 weeks, treatment adherence is monitored by asking at what times the capsules are ingested and whether the participant experiences any side effects. Study participants are asked to contact one of the researchers with any questions about the study medication during the treatment period. The drug monitoring is performed by one of the researchers or by the research nurse who will also perform the follow-up outcome measurements. If necessary, the treating physician is consulted.

At 4 weeks, the participant will return the study medication bottle after which any leftover medication is counted. The number of unused capsules and the reason for possible non-compliance (if one or more capsules are returned) is registered in the designated case report form.

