### Plans to promote participant retention and complete follow-up {18b}

Study follow-up is performed at 4, 8 and 12 weeks with an outpatient clinic visit and CT scan. During these visits, all outcome measurements are performed by one of the researchers. To maximise participant retention, this study follow-up is parallel to the regular follow-up in the outpatient clinic by the treating physician (standard treatment). Also, we incorporate an extra telephonic interview after 2 weeks to monitor drug adherence and adverse events. Study treatment is limited to a maximum of 28 days and to a maximum of 56 capsules, regardless of whether a deviation from the study protocol occurs. In case of a protocol violation, study follow-up will remain unchanged.

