## Discussion

Optimal treatment for chronic subdural haematoma remains a matter of debate. Currently, the only effective treatment is surgical evacuation of the haematoma. In these old, often frail patients however, surgery comes with significant morbidity and mortality [9]. The quest for a non-surgical treatment has not yet resulted in an effective therapy. First reports on the use of TXA seem promising however [10–16]. This randomised controlled trial is meant to determine the efficacy of TXA as an addition to a primary conservative treatment of cSDH, in an effort to prevent surgery for cSDH.

Our study has several strengths. First, it tests the efficacy of TXA versus placebo during a conservative treatment of cSDH in an effort to prevent progression of the haematoma and with that, to prevent the necessity of a surgical treatment. Since progression of the haematoma is expected in the first weeks after diagnosis, study treatment is carried out during this period. Second, our primary endpoint is a clinical parameter instead of a radiological, in contrast to the two other currently running trials. This is important, because failure of the conservative treatment and the decision to perform an operation is based on clinical signs and symptoms and not so much on radiological parameters. Because we do think that radiological follow-up is important in the conservative treatment, we added it as a secondary outcome parameter. Third, we also added outcome parameters that measure cognitive function, functional outcome, quality of life and healthcare-related costs. All of these have only sparsely been reported in current literature. Fourth, we include mentally incompetent patients and patients using anticoagulants and antiplatelets which comprise a significant part of the target population. If we would not include them, it would be difficult to extrapolate the results of this study to the total group of patients with cSDH. Fifth, this study protocol does not interfere with our regular conservative treatment in which we monitor cSDH patients regularly and switch to a surgical if the symptoms worsen or do not recover. Finally, TXA is a safe drug with minimal side effects: most importantly, there is no evidence of an increased risk of thromboembolic complications when using TXA.

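### The adverse-event section relies on spontaneous reports, which conflicts with the questioning described elsewhere, and no adverse-event question is stated after week 4

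*Protocol article*

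**What the plan says.** The protocol article describes adverse-event collection in three places.

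- **Adverse event reporting and harms {22}, Reporting.** Because most of the study takes place at home, "Getting knowledge of AEs depends on spontaneous reporting by the subject or other treating physicians". Events are to be reported over the 12-week study period, and up to 6 months for participants who opt in to the later telephone measurement. Every reported event goes into the CRF.
- **Plans to promote participant retention {18b}.** Besides clinic visits with a CT scan at 4, 8 and 12 weeks, where a researcher performs the outcome measurements, "we incorporate an extra telephonic interview after 2 weeks to monitor drug adherence and adverse events".
- **Strategies to improve adherence {11c}.** At 2 and 4 weeks adherence is monitored "by asking at what times the capsules are ingested and whether the participant experiences any side effects".

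The (Serious) adverse events subsection defines an adverse event broadly, as any undesirable experience during the study regardless of a presumed link with the product. The background section states that "a prospective study evaluating the efficacy and safety of TXA is needed", and the Discussion counts as a strength that "we include mentally incompetent patients and patients using anticoagulants and antiplatelets which comprise a significant part of the target population".

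**The concern.** A site reading these sections cannot tell whether adverse events are to be asked for or waited for. The section that governs safety reporting describes only unsolicited reports. The sections on adherence and retention describe questions.

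The stated questions also leave gaps. They fall at 2 and 4 weeks, while the reporting period runs to 12 weeks or 6 months. The week-4 question concerns side effects, which asks the participant to judge whether the drug was the cause; the protocol's own definition does not require that. A participant with a leg thrombosis or a first seizure might not call it a side effect. The Reporting section names the subject and other physicians as sources, but not a representative, although the trial enrols some participants who cannot consent for themselves.

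At stake is the completeness of the safety data that the DSMB reviews and that would accompany the registration of a new indication, which the Objectives section foresees. No later analysis can recover events that were never collected.

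**Working it through.** **1. The statements side by side**

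| Contact | Adverse-event question stated? | Section |
|---|---|---|
| 2-week call | Yes: adverse events; side effects | {18b}; {11c} |
| 4-week visit | Yes: side effects | {11c} |
| 8-week visit | None stated | {18b} |
| 12-week visit | None stated | {18b} |
| 6-month call (optional) | None stated | {22} |
| Whole reporting period | Spontaneous report | {22} |

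Treatment lasts 28 days, so the stated questions cover the exposure period. The reporting period is longer. The reason given for relying on spontaneous reports, that patients are at home, does not apply at the scheduled contacts.

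**2. The plan's own figure**

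The article gives no precision or power for harms. The relevant figure is the arm size. Exact power of Fisher's test for 75% v 50% (two-sided 0.05) is 79.4% at 63 per arm and 80.2% at 64. Then 64/0.92 = 69.6, rounded up to 70. The stated 70 per arm reproduces.

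**3. Inputs for the size of the problem**

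- n = 70 per arm (Sample size {14}).
- Event risk p: 2%, taken from the 1.7% (TXA) and 2.0% (placebo) vascular occlusive rates in the Risks section; 5% and 8% are assumptions.
- Capture fraction c: 50%, 70% and 95% are assumptions, because the article gives none; 100% is the ideal.

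**4. Chance that an arm records no event: (1 − p·c)^70**

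| True risk | c = 50% | c = 70% | c = 95% | c = 100% |
|---|---|---|---|---|
| 2% | 49% | 37% | 26% | 24% |
| 5% | 17% | 8% | 3% | 3% |
| 8% | 6% | 2% | 0.4% | 0.3% |

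For example, at 2% and c = 50%: 0.99^70 = 0.495.

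**5. What zero recorded events would show**

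The exact two-sided 95% upper limit for 0/70 is 1 − 0.025^(1/70) = 5.1%. This limits p·c, so the limit for the true rate is 5.13%/c: 5.4% at c = 95%, 7.3% at 70% and 10.3% at 50%.

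**6. Effect on the comparison between arms**

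With equal capture in both blinded arms, the expected risk difference is c(p₁ − p₀) and the ratio of recorded risks is p₁/p₀. Take an assumed 6% v 2%:

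- c = 100%: expected events 4.2 v 1.4, difference 4 points, ratio 3.
- c = 50%: expected events 2.1 v 0.7, difference 2 points, ratio 3.

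The approximate standard error of the log ratio, √(1/a + 1/b − 2/70) at the expected counts a and b, rises from 0.96 to 1.37. The standard error of the difference falls from 3.3 to 2.4 points, but the difference falls faster: the ratio of difference to standard error drops from 1.21 to 0.85. These approximations are rough at such small counts; the direction is what matters.

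**7. Limit set by sample size**

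Exact Fisher power at 70 per arm with full capture is 8% for 2% v 6%, 36% for 2% v 10% and 74% for 2% v 15%. For the last contrast, power falls to 49% at c = 70% and 27% at c = 50%. At least 6 events against 0, or 8 against 1, are needed for p < 0.05.

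**The case against.** A reader might infer that nobody asks about harms, or that the trial compares no harms between arms. The article does not support either reading.

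- **Patients are asked.** The 2-week call and the 4-week question fall within the 28-day treatment period. The spontaneous-report sentence may have been meant only for events between contacts, but it carries no such limit. The conflict in wording therefore stands.
- **Weeks 8 and 12 are not silent.** CT and mNIHSS at these visits bear on new intracranial bleeding and stroke. Falls and deaths are registered, and healthcare use is collected by questionnaire up to 6 months. This is a fair limit on the point, but none of it is an adverse-event question, and it would detect a peripheral thrombosis or a seizure only indirectly.
- **Some harms are compared.** Falls and mortality are tested between arms, and the DSMB reviews unblinded safety data after 35, 60 and 105 participants. Further analyses are left to an SAP that is not shown, so the absence here of a thromboembolic or seizure comparison is not an error. How events are collected, however, is a protocol matter.
- **The size is uncertain.** A capture rate of 50% may be too low for clinically evident thrombosis, since many such events would be serious and could reach the investigators through treating physicians. The 5% and 8% risks exceed the article's cited 1.7–2.0%. At 2% and 95% capture, zero recorded events still has a 26% chance, so better questioning would not overcome the small sample.
- **The population is mildly affected.** Entry requires a GCS of at least 14 and an mNIHSS of at most 4. Randomisation is stratified by antithrombotic use, so its withdrawal should not differ systematically between arms. Difficulty in volunteering events is therefore a concern for some participants, not for most.

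**Conclusion.** The point holds as an inconsistency with a gap. The Reporting section conflicts with the retention and adherence sections on whether adverse events are solicited. No question is stated for 8 weeks, 12 weeks or the optional 6-month call, although events are reportable then. The side-effect question is narrower than the protocol's definition of an adverse event.

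The consequence is possible undercounting in both arms. If capture is equal, that shrinks the absolute difference, leaves the expected ratio unchanged and makes both harder to estimate. The size cannot be fixed from the article. At a 2% risk, moving from an assumed 50% to 95% capture lowers the chance of recording no event from 49% to 26%. Much of the difficulty in detecting rare harms comes from having 70 per arm and would remain. It would go too far to conclude that harms go unasked, or that a safety comparison is missing from the trial's full plan. The change is worth making because it is cheap.

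**What to change.** - Replace the spontaneous-report sentence in the Reporting section with one method that agrees with {11c} and {18b}. At each existing contact (2, 4, 8 and 12 weeks, and 6 months where opted in), blinded staff ask every participant, or their representative, a fixed adverse-event question. It should follow the protocol's own definition and name thromboembolic events, stroke, seizure and new bleeding. Spontaneous reports between contacts continue to count.
- If the SAP does not already do so, report these events by arm as counts with a risk difference and exact 95% confidence interval, without a significance claim.

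**Cost:** one CRF page and a few minutes at contacts that already take place, with no extra visits. The downside is that more minor events will be recorded in both arms. For participants already followed up under the present wording, record the date of the change so that the two collection periods can be told apart.
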